## Abstract

**Background:**

Chronic obstructive pulmonary disease (COPD) is recognized as a systemic illness with significant extra-pulmonary features, such as exercise intolerance and muscle weakness. Pulmonary rehabilitation has been shown to be very effective in counteracting these consequences in patients with more advanced COPD. However, limited data is available on the efficacy of a physical exercise training programme in patients with mild to moderate COPD in primary care. Furthermore, it is unknown if improved exercise capacity translates into enhanced daily physical activities. The aim of this paper is to describe the design of a randomized controlled trial to assess the efficacy of a physical exercise training programme in patients with mild to moderate COPD.

**Methods/design:**

In this randomized controlled trial situated in the primary care setting, 102 patients with mild to moderate airflow obstruction (FEV_1_ ≥ 50% of predicted), dyspnoea and a physically inactive lifestyle will be randomized to an intervention or control group. The intervention group receives a 4-month physical exercise training programme at a local physiotherapy practice, which includes exercise training, resistance training, breathing exercises and advises on how to increase the level of physical activity. The control group receives usual care, i.e. advises on how to increase the level of physical activity and a sham treatment at a local physiotherapy practice of which no physiological training stimulus can be expected. Primary outcome is functional exercise capacity at 4-months measured on the six-minute walk distance. Secondary outcomes include peripheral muscle strength, physical activity in daily life, health related quality of life, Medical Research Council (MRC) dyspnoea score and patients’ perceived effectiveness. Follow-up measurement will take place at 6 months after baseline.

**Discussion:**

This will be one of the first studies to evaluate the efficacy of a physical exercise training programme in patients with mild to moderate COPD completely recruited and assessed in primary care. The results of this trial may give a unique insight into the potential of the implementation of an easy, close-to-home rehabilitation programme.

**Trial registration:**

The Netherlands National Trial Register NTR1471.

## Background

In patients with chronic obstructive pulmonary disease (COPD), disease severity and prognosis are not only determined by lung function impairment, but are also related to extra-pulmonary consequences of COPD such as muscle weakness and exercise intolerance [1–3]. The exercise training component of pulmonary rehabilitation (PR) has been shown to be very effective in improving exercise capacity, dyspnoea and quality of life [4]. As a result, for patients with moderate to very severe COPD and breathlessness (MRC dyspnoea score >2) exercise training is recommended as part of PR in national and international guidelines [1, 5]. Another extra-pulmonary feature of COPD is the decline in daily physical activity (PA) [6]. Only a few trials have investigated the effect of exercise training on changes in daily physical activity [7–11]. These studies showed contradictory results, ranging from significant improvements in PA [8, 9] after exercise training, to small or moderate effects [7, 10] and no effects at all [11]. Overall, current data indicate that exercise training results in a significant but small effect on PA and that larger randomized controlled trials (RCT’s) are needed in this area [12].

A differentiation should be made in the improvement of exercise capacity on the one hand and improvement of daily physical activity on the other. Improvement in exercise capacity fulfils the short-term goal of reducing breathlessness and fatigue [11], improving muscle strength and thus lowers the barriers to be physically more active [10]. Regular physical activity in COPD patients has important long-term health-related benefits, like a lower risk of COPD related hospital admissions and decreased mortality [13]. Furthermore, low physical activity has been associated with systemic inflammation, cardiac dysfunction and lung function decline [13, 14].

All abovementioned studies were performed in a clinical or rehabilitation setting in COPD patients in more advanced GOLD stages [4]. However, patients with moderate COPD also have impairments in exercise capacity, respiratory muscle function, limb muscle force and quality of life [15–18]. In addition, the level of physical activity is already decreased in patients with moderate COPD compared to healthy control subjects [14, 19, 20]. Scant information is available on the effects of community-based exercise training programmes in general and even less about their effect on daily activity [9]. Exercise training programmes in patients with moderate to severe COPD, when incorporated in (self)-management or integrated disease management programmes in primary care, result in improvements in health-related quality of life, breathlessness, exercise capacity, muscle strength, daily physical activity, reduced hospital admissions and hospital days per person [9, 21–24]. Recruitment and assessment was done in the respiratory department of general hospitals [9, 21] or the intervention was multifaceted (i.e. involved more than exercise therapy alone) [22]. To our knowledge hardly any data are available on the efficacy of physical exercise training programmes in patients with mild to moderate COPD that are recruited and treated solely in primary care.

### Relevance

From a patients’ perspective, an increase in exercise capacity and daily physical activity during the early stage of the disease could be beneficial in order to stop the downward spiral of symptom-induced inactivity, deconditioning, muscle weakness, the fear of movement and reduced quality of life. Since behavioural research suggests that modifying behavioural patterns and coping styles takes time to be effective, regular exercise should be started early in the course of the disease for maximal effect [25]. It seems advantageous to initiate exercise training when the symptoms of dyspnoea and deconditioning are not very pronounced. Furthermore, it is proposed that in patients with a relatively preserved lung function, the physiological reserve for improvement is much larger than in patients with (very) severe disease [22].

Treatment of COPD at an early stage could also lessen the burden of disease for society [26]. COPD is one of the leading causes of morbidity and mortality worldwide and imparts a substantial economic burden [27]. COPD-related illness costs are disproportionately distributed, with 10% of the patients (mostly patients in the more severe stages of the disease) accounting for 73% of the total costs, in which hospitalization is the largest contributor [27]. An exercise training programme in primary care will be a relatively cheap and an easily accessible intervention for more patients than an expensive hospital-based rehabilitation programme [28]. Although longitudinal studies are lacking, it is suggested that early recognition of progression of exercise impairment especially in less advanced COPD patients is relevant to prevent further deterioration of functional capacity [22, 29].

### Current daily care for COPD

The Practice Guideline COPD of the Dutch College of General Practitioners (NHG standard, 2007) recommends general practitioners (GP’s) advise all patients with COPD to be sufficient physically active [5]. Referral to a physical exercise training programme in a physiotherapy setting is advised only in patients with moderate to severe COPD, who have impairments in physical functioning due to dyspnoea. As of 2010, there is a new development in the primary care organization of patients with chronic disease in the Netherlands, including COPD. Disease management programmes have regionally been developed by general practitioners in collaboration with other caregivers in primary care. General practitioners and/or the nurse practitioner have a central role. Their COPD care entails lung function testing, prescription of pharmacotherapy and counselling on smoking cessation, inhalation technique and physical activity. There is the possibility to refer patients with mild to moderate COPD to registered physiotherapists, experienced in COPD care. The implementation of this disease management programme for COPD is encouraged by the reimbursement through so-called chained diagnose-treatment combination (DTC) [29]. Although in some regions in the Netherlands these disease management programmes for COPD are already implemented and serve as current daily care, no evidence on the effectiveness of these programmes is available. In addition, no data are available on the added value of a physical exercise training programme compared to advice on increasing daily physical activity in usual care.

### Objectives

The primary objective of our study is to evaluate the *efficacy* of a physical exercise training programme (PETP) in patients with mild to moderate COPD in the primary care setting on exercise capacity, physical activity, dyspnoea and quality of life. The 6 month time point is aimed at gaining more insight into the lasting of the effects.

The secondary objective is to assess how patient characteristics and baseline burden of disease modify the effect of a physical exercise training programme on functional exercise capacity in patients with mild to moderate COPD in primary care.

## Methods/design

### Study design

A randomized controlled trial performed in the primary care setting in which the effects of a 4-month physical exercise training programme for patients with mild to moderate COPD will be compared to a control programme. The latter includes advices concerning physical activity according to the Practice Guidelines of the Dutch College of General Practitioners [5] and a sham-treatment (ST) in physiotherapy practice.

General practice is the primary entrance for patients to participate in the trial. If a patient is a potential trial participant, the GP or nurse practitioner explains to the patient that it is important to enhance his physical activity level. For professional support to achieve this goal, the patient is referred to a COPD-certificated physiotherapist. If the patient is willing to undergo the physiotherapy treatment, he/she makes an appointment at the physiotherapy practice. The physiotherapist will give extensive information about the study procedures and the patient will have one week to consider participation in the trial. If the patient wants to participate, randomization will take place after obtaining informed consent. Patients of both treatment groups will be assessed in physiotherapy practice at baseline, at the end of the programme (after four months) and six months after baseline assessment. The measurements done by the physiotherapist are part of their routine assessments and are imbedded in the intake procedures. The results of this intake procedure will be the starting point of the treatment. Figure 1 illustrates the flow of the study.

**Figure 1 Fig1:**
[figure not shown]
**Overview of the flow of the study.**

The ethics committee of Maastricht University has approved the study protocol, procedures and informed consent and the trial has been registered at The Netherlands National Trial Register NTR1471.

### Setting

This multicenter trial is coordinated by the CAPHRI School for Public Health and Primary Care of Maastricht University and conducted in several general practices and physiotherapy practices in the southern part of the Netherlands.

### Study population

Participants for the trial will be recruited from general practices in Limburg, in the southern part of the Netherlands. There are 614 general practices in this region covering a population of over 1.000.000 [30]. Statistics suggest that 1,7% of the Dutch population is likely to have COPD [31]. The population in Limburg is the least physically active population of the Netherlands [32].

Inclusion will be based on patients with a clinical diagnosis of mild to moderate COPD (post-bronchodilator FEV_1_/FVC ratio < 0,7 and FEV_1_ ≥ 50% of predicted); who not have a minimum of 30 minutes of physical activity at moderate intensity, on at least 5 days per week, according to the ACSM-recommendation [33]; having a stable situation (no exacerbations in the last 8 weeks) and adequate and optimal inhalation technique, are competent enough to understand and speak the Dutch language and having provided written informed consent. According to the Practice Guidelines of the Dutch College of General Practitioners, a maximal cardiopulmonary exercise test prior to exercise training will be conducted by a pulmonologist, cardiologist or a sports medicine physician in COPD patients who suffer from cardiopulmonary co morbidities [5, 34].

Patients will be excluded from the trial, when they: already receive or have received a physical exercise training programme or rehabilitation therapy in the past year; have had respiratory tract infections within the last 8 weeks; are suffering from serious co morbid conditions, which would interfere with regular exercise training (including severe orthopaedic, muscular, neurological disorders or cardiovascular conditions) and patients who are expected to be lost for follow-up (e.g. because of a planned change of residency or a long holiday break).

### Randomization and blinding

After informed consent is obtained, patients will be randomly assigned to the intervention group or the control group in a 1:1 ratio, with the help of computer generated random number tables. Randomization will be performed by a centralized and independent person who has a concealed list. The researcher is not involved in allocation to treatment group or setting. Full blinding procedures are not applicable in this study. The participating general practitioners, nurse practitioners and physiotherapists and also the patients cannot be blinded to allocation of individuals to the intervention group or control group. Although patients will be aware of the existence of two treatment arms, they are not informed about the exact content of the other treatment arm. Also, patients of both groups will not be in the same physiotherapy setting for treatment at the same time. The researcher will be fully blinded to the randomization list until the clinical database is unlocked at the end of the trial.

### Sample size calculation

We performed a pilot study in one physiotherapy setting in order to get a rough idea of the improvement in six-minute walk distance (6MWD) in this group of patients after a 4-month physical exercise training programme. Data of six patients with mild to moderate COPD were collected. Their mean 6MWD was 475 metres with a standard deviation of 62. These patients increased their 6MWD by a mean of 52 metres. Troosters et al. reported a mean difference in change from baseline of 52 metres between the intervention group and control group, in a study of the short- and longer-term benefits of 6 months pulmonary rehabilitation [35]. A more recent study showed an improvement of 54 metres with a standard deviation of 78 metres after a 7 week pulmonary rehabilitation programme [11]. Our assumptions for this study are that the mean difference in change from baseline between the intervention group and the control group (δ) is 52 metres (52–0 m), with a standard deviation (σ) of 78 metres [11]. According to the effect size measures for two independent groups this implies a large effect size (Cohen’s d = δ/σ = 52/78 = 0.66) [36]. The sample size needs to be 36 patients per treatment arm (72 in total), whereby α = 0.05 (2 tailed), 80% power and a ratio of control to experimental patients of 1:1. This sample size calculation is done by using the PS power and sample size program of Dupont and Plummer [37, 38].

A total patient number of 102 participants (51 per treatment arm) is needed, based on the abovementioned calculation and allowing for dropouts (30%). Previous studies showed a drop-out rate varying from 26 to 31% [11, 35, 39, 40].

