The physical exercise training programme will consist of two supervised sessions per week in the physiotherapy setting in primary care. These sessions will be with 1–5 patients at the time and the duration of each session will be 60–90 minutes, depending on group size. From an organisational and practical point of view it is not feasible to ask patients to come to a physical therapy setting more often. Furthermore, as mentioned before, an important part of the programme is enhancement of daily physical activity. So, patients are requested to perform an additional training session at home, including walking and/or cycling and they have to report these activities weekly to the physiotherapist. It is our aim to enhance the awareness and responsibility of our patients to change their physical activity behaviour for the long term and this encompasses enhancement of self-management and self-efficacy.

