### Data analysis

The descriptive characteristics will be presented quantitatively as means (±standard deviation) for continuous variables and as medians for categorical variables and will be presented for the total group, as well as for the separate groups. Unpaired t-tests will be used to compare the effects of the treatment between the intervention group and control group at the end of the physical exercise training programme (4 months). P-values smaller than 0.05 will be considered as statistically significant.

Group (intervention vs. control) by time (pretest vs. posttests) repeated measurements analysis of variance (RM ANOVA) will be performed to examine (1) intervention main effect, (2) time main effect, and (3) intervention by time interaction effect on each of the continuous primary and secondary outcomes. An analysis of covariance will be done to evaluate the relationship between covariates and the dependent variable. The random effect will also be evaluated, since participants from both arms will be nested within the same physiotherapy setting. To evaluate which factors predict a positive outcome, i.e. the physical exercise training programme is effective, a multiple linear regression analysis will be done, using interaction terms between predictors and physical exercise. A predictor variable will make a significant contribution to predicting the outcome when P-value is smaller than 0.05. The following possible predictors are taken into account, baseline: MRC dyspnoea score, walking distance, peripheral muscle strength, level of daily physical activities and compliance with the training programme [62–64].

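### With 30% dropout expected, the two named comparisons of six-minute walk distance by default omit patients with missing values, and can rest on different patients

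*Protocol article*

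**What the plan says.** Sample size calculation (protocol article) arrives at the evaluable number: "The sample size needs to be 36 patients per treatment arm (72 in total"). It then raises this to 102, or 51 per arm, "based on the abovementioned calculation and allowing for dropouts (30"%), and cites earlier studies with dropout of 26 to 31%.

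The primary outcome is the increase in 6MWD from baseline to 4 months (Primary outcome measure). Outcomes are measured at baseline (T0), 4 months (T1) and 6 months (T2) (Outcome measures).

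Data analysis names two comparisons of the arms. First: "Unpaired t-tests will be used to compare the effects of the treatment between the intervention group and control group at the end" of the programme, at 4 months. Second, a group-by-time "repeated measurements analysis of variance (RM ANOVA) will be performed" for each continuous primary and secondary outcome, with a time factor that covers baseline and the later measurements. An analysis of covariance and a random effect follow. The reason given for the random effect is that patients of both arms are nested within physiotherapy practices.

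The arms differ in what they ask of patients. For the intervention, "The physical exercise training programme will consist of two supervised sessions per week", each lasting 60 to 90 minutes, with a further session at home. The control arm attends once a week for 30 minutes at low exertion (Control group).

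**The concern.** The plan expects to lose nearly a third of its patients, yet it names two methods that, in their usual form, cannot use a patient with a missing value. The enlarged sample protects power. It does nothing against bias if those who leave differ from those who stay.

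A link between dropout, arm and outcome is plausible here. The training arm demands more than twice the supervised time plus work at home, and Potential barriers names lack of time and no felt need for training as obstacles in this population. Patients and physiotherapists know the allocation, and the treating physiotherapists take the measurements at the practice (Study design; Bias, confounders and limitations). A patient who stops attending could therefore easily miss the assessment as well. If so, the comparison is between those who finished a demanding programme and those who finished a light one, and randomisation no longer guarantees that they are alike.

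A second problem is that the two analyses of the same outcome need not use the same patients, so a difference between their results would be hard to interpret.

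**Working it through.** **1. The plan's own figures.** Inputs from Sample size calculation: "the mean difference in change from baseline between the intervention group and the control group (δ) is 52 metres", "with a standard deviation (σ) of 78 metres", and "whereby α = 0.05 (2 tailed), 80% power and a ratio of control to experimental patients of 1:1".

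- n per arm = 2 × (1.960 + 0.842)² × (78/52)² = 2 × 7.85 × 2.25 = 35.3, rounded up to 36. Total 72, as stated.
- Inflation: 72/0.70 = 102.9, against 102 stated. The difference is rounding.

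**2. Expected loss.**

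- At 30%: 0.30 × 102 = 30.6 patients, leaving 71.4, or 35.7 per arm.
- At the cited 26% and 31%: 26.5 and 31.6 patients.
- Power of the t-test on those remaining (noncentral t, 52 m, SD 78 m): 81.5% at 26% loss, 79.3% at 30%, 78.7% at 31%. The allowance does its job for power.

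**3. Who enters each analysis when nothing is imputed.**

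| 6MWD available | t-test at 4 months | RM ANOVA over T0, T1, T2 | Mixed model, baseline-adjusted |
|---|---|---|---|
| T0, T1, T2 | yes | yes | yes |
| T0, T1 | yes | no | yes |
| T0, T2 | no | no | yes, through the T1–T2 correlation |
| T0 only | no | no | adds almost nothing |

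The second row is where the two named analyses part. The article does not split the 30% by visit. If it is the loss by 4 months, the ANOVA may hold fewer than 71 patients. If it is the loss by 6 months, the t-test may hold more.

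**4. How far a completer estimate could lie from the effect in all randomised patients.** Assume 30% loss in each arm, a completer effect of 52 m, and mean changes P and C in the training-arm and control-arm dropouts. Then

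effect in all randomised = 0.70 × 52 + 0.30 × (P − C).

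- P = 0, C = 0: 36.4 + 0 = 36.4 m.
- P = 26, C = 0: 36.4 + 7.8 = 44.2 m.
- P = 52, C = 0: 36.4 + 15.6 = 52.0 m, no distortion.
- P = 52, C = −26: 36.4 + 23.4 = 59.8 m, a shift the other way.

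No value of P or C is in the article. These lines show a range, not an estimate.

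**The case against.** The strongest reply is that the article nowhere restricts the analysis to complete cases. It names tests, and either test can be run on imputed data. Analysis sets and missing-data rules are commonly left to a full protocol or SAP, which is not shown, so their absence is no fault. Planning for attrition does not commit a trial to analysing completers only. This stands. A reader might infer that the plan discards 30 patients, but the text supports only that the named methods leave out incomplete patients by default.

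Further points also stand:

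- Study design and Outcome measures schedule the 4- and 6-month assessments for patients of both groups and do not limit them to those still attending. Patients who stop treatment but are measured would be in the t-test, and fewer than 30 would be lost.
- Study population excludes patients expected to be lost to follow-up, a partial safeguard.
- A missing 6-month value does not remove anyone from the 4-month t-test.
- A reader might infer that the bias favours training. The article gives no dropout by arm, and control patients may also leave an unrewarding sham.
- A mixed model alone would not recover the effect in patients with baseline data only.

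One part carries less weight. The random effect leaves room for a mixed model, but its stated purpose is clustering by practice, not incomplete follow-up.

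**Conclusion.** The point holds as a mismatch between a stated expectation and stated methods, not as a complaint about missing detail. About 30 of 102 patients are expected to drop out, and the two named comparisons by default omit patients with missing values, each by a different rule. If dropout is related to arm and outcome, which the unequal burden makes plausible, the comparison may be biased. The direction and size are not established: the figures of 36 m and 44 m depend on assumed changes in dropouts, and other assumptions give no shift or the opposite one.

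The count of 30 applies to an analysis only if every dropout lacks the value that it needs. The sample size is not in error. This is a worthwhile, inexpensive improvement, best made before the database is unlocked.

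**What to change.** - For 6MWD, replace the t-test and the RM ANOVA with one likelihood-based mixed model for repeated measures. Include all randomised patients as allocated, adjust for baseline 6MWD, use every available T1 and T2 value, and make the 4-month contrast primary. The random effect for physiotherapy practice can stay in this model.
- State that the T1 and T2 assessments already scheduled apply also to patients who stop attending sessions. This does most to reduce the problem, because it turns stopping treatment into something other than missing data.
- Add one missing-not-at-random sensitivity analysis, for example with missing training-arm values imputed from the control mean change. The mixed model assumes that missingness depends only on observed data, so by itself it does not protect against dropout related to unseen outcomes.

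The cost is slightly more analysis work, some assessments of patients who have stopped sessions, and a possibly less favourable estimate. The number to randomise stays at 102.
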